## STATEMENT OF COMPLIANCE

This study will be conducted in compliance with the International Council for Harmonisation of Technical Requirements for Pharmaceuticals for Human Use (ICH) E6(R2) Good Clinical Practice (GCP) guidelines and the applicable regulatory requirements at participating institutions.

# PROTOCOL SUMMARY

## Synopsis

| **Title:** | Investigation of Immune Amnesia Following Measles Infection in Select African Regions |
| --- | --- |
| **Study Description:** | This is a prospective, observational, longitudinal study to be conducted in West Africa to investigate the effects of measles virus (MeV) infection on pre-existing immunity, vaccine response, and susceptibility to subsequent illness. Eligible children will be enrolled into 1 of 2 arms: acute MeV infection (cases) or no acute MeV infection (controls) as assessed using upper respiratory specimens and blood samples. Blood samples will be collected at Screening/Enrollment (Day 0), optional repeat IgM serology for inconclusive or negative Day 0 results (Day 7-10), and follow-up visits on Day 14, Week 13, and Week 52. The blood samples will be tested for humoral and cellular immune responses to endemic pathogens to determine changes in antibody diversity and antibody secreting cells (ASCs). All children in each arm will receive rabies vaccination (standard 3-dose series given as pre-exposure prophylaxis [PrEP]), with the first dose randomized to either Week 8 or Week 47 after enrollment. Biological samples will be collected after vaccination to assess if the immune stimulus (rabies vaccine) response differs: 1) between children with and without MeV infection, and 2) based on the timing of the receipt of the rabies vaccine. The study team will collect, to the extent possible, information on healthcare encounters for evaluation and treatment of illness during the year-long follow-up to determine if there is a difference in the number of encounters by study group. |
| **Objectives:** | Primary Objectives   1. To determine if MeV infection induces a loss of pre-existing immunity (immune amnesia) to endemic pathogens at Week 13 after baseline in children in select African regions. 2. To determine the effect of MeV infection on immune response to a controlled immune stimulus (rabies vaccination) at early and late timepoints post-infection.   Secondary Objectives   1. To determine if there is an increase in the healthcare system encounters in the year following enrollment in children with recent MeV infection compared to those without recent MeV infection. 2. To determine if MeV infection induces a loss of pre-existing immunity (immune amnesia) to endemic pathogens at Week 52 after baseline in children in select African regions.   Exploratory Objectives   1. To assess the appearance and continued production of B and T cells, especially ASCs from peripheral blood mononuclear cells (PBMCs) in circulation following MeV infection in children 1-15 years old in a subset of participants depending on availability of collected blood samples. 2. To attempt to identify the etiology of illness in children who present with signs and symptoms consistent with measles and are screened but not enrolled due to negative measles polymerase chain reaction (PCR) and immunoglobulin M (IgM). 3. To identify the genotypes of MeV collected in the study. 4. To characterize the phenotype of the rash and/or Koplik spots in children who present with signs and symptoms consistent with measles who test positive for measles (PCR and/or IgM positive) and who test negative for measles (PCR and IgM negative). |
| **Accrual Ceiling:** | A maximum of 500 across all study sites. |
| **Study Population:** | We will enroll approximately 256 children aged 1-15 years into 1 of 2 study groups:   - Group 1 (Cases): acute MeV infection (n=128) with approximately n=64 age 1-5 years and approximately n=64 age 6-15 years, and each age group randomized 1:1 to receive rabies vaccine at Week 8 or Week 47 after enrollment - Group 2 (Controls): no acute MeV infection (n=128) with approximately n=64 age 1-5 years and approximately n=64 age 6-15 years, and each age group randomized 1:1 to receive rabies vaccine at Week 8 or Week 47 after enrollment |
| **Description of Sites/Facilities Enrolling Participants:** | The study is expected to take place in a subset of the NIAID Division of Clinical Research (DCR) Special Projects sites and any additional site(s) that may be identified. |
| **Participant Follow up:** | 12 months. |
| **Study Duration:** | Up to 48 months. |

## Schema

### Cohorts

|  |
| --- |

Figure 1: Study cohorts

### Timing of visits

[figure not shown]

Figure 2: Timing of visits with associated procedures

## Schedule of Activities

Table 1. Schedule of study evaluations and procedures.

|  | **Visit 0** | **Visit 0.1** | **Visit 1** | **Visit 2^a^** | **Visit 3^a^** | **Visit 4^a^** | **Visit 5** | **Visit 6** | **Visit 7** | **Visit 8^b^** | **Visit 9^b^** | **Visit 10^b^** | **Visit 11** |
| --- | --- | --- | --- | --- | --- | --- | --- | --- | --- | --- | --- | --- | --- |
| **Evaluation/**  **Procedure** | **Screening/ Enrollment^c^ Blood Draw** | **Serology repeat (Retest for measles IgM)** | **Randomization**  **Blood Draw** | **Early rabies vaccine Dose 1** | **Early rabies vaccine Dose 2** | **Early rabies vaccine Dose 3** | **Blood draw**  **Healthcare Ques** | **Healthcare Ques** | **Healthcare Ques** | **Late rabies vaccine Dose 1** | **Late rabies vaccine Dose 2** | **Late rabies vaccine Dose 3** | **Blood draw**  **Healthcare Ques** |
| **Timepoint**  **(Window)** | **Day 0^c^** | **Day 7-10^c^** | **Day 14^c^**  **(±2 days)** | **Week 8**  **(±3 days)** | **Week 9**  **(+2 days)** | **Week 11-12** | **Week 13**  **(+3 days)** | **Week 26**  **(±2 weeks)** | **Week 39**  **(±2 weeks)** | **Week 47**  **(±3 days)** | **Week 48**  **(+2 days)** | **Week 50-51** | **Week 52**  **(+3 days)** |
| Informed consent/assent | X |  |  |  |  |  |  |  |  |  |  |  |  |
| Inclusion/ Exclusion^c^ | X | | |  |  |  |  |  |  |  |  |  |  |
| Vital signs^d^ | X |  | X | X^d^ | X^d^ | X^d^ | X | X | X | X^d^ | X^d^ | X^d^ | X |
| MUAC^e^, height, weight | X |  |  |  |  |  |  |  |  |  |  |  | X |
| Demographics | X |  |  |  |  |  |  |  |  |  |  |  |  |
| Upper respiratory specimen (OP/NP swab) for measles PCR | X |  |  |  |  |  |  |  |  |  |  |  |  |
| HIV^f^ | X^g^ |  |  |  |  |  |  |  |  |  |  |  | X^f^ |
| Hemoglobin level^h^ | X |  | X |  |  |  | X |  |  |  |  |  | X |
| Urine pregnancy test^h^ | X^i^ |  | X | X^i^ | X^i^ | X^i^ | X |  |  | X^i^ | X^i^ | X^i^ | X |
| Measles IgM/IgG | X^g^ | X |  |  |  |  |  |  |  |  |  |  |  |
| Medical history | X |  |  |  |  |  | X |  |  |  |  |  | X |
| Concomitant medications | X |  | X | X | X | X | X | X | X | X | X | X | X |
| Physical examination | X |  | X |  |  |  | X | X | X | X |  |  | X |
| Optional photography (skin rash and Koplik spots)^j^ | X |  |  |  |  |  |  |  |  |  |  |  |  |
| Randomization to early or late rabies vaccine |  |  | X |  |  |  |  |  |  |  |  |  |  |
| Measles vaccine^k^ |  |  | X |  |  |  |  |  |  |  |  |  |  |
| AE assessment |  |  | X | X | X | X | X | X | X | X | X | X | X |
| Healthcare Utilization Questionnaire |  |  |  |  |  |  | X | X | X |  |  |  | X |
| Rabies vaccine |  |  |  | (X) | (X) | (X) |  |  |  | (X) | (X) | (X) |  |
| Research blood collection^l^ | X |  | X |  |  |  | X |  |  |  |  |  | X |
| Vitamin A | X^m^ |  |  |  |  |  |  |  |  |  |  |  |  |

Abbreviations: AE, adverse event; HIV, human immunodeficiency virus; Ig, immunoglobulin; MUAC, mid-upper arm circumference; NP, nasopharyngeal; OP, oropharyngeal; PCR, polymerase chain reaction.

(X) = Each participant will receive only one 3-dose series of rabies vaccine according to randomization to early group (vaccination at Visits 2, 3, and 4) or late group (vaccination at Visits 8, 9, and 10).

^a^ EARLY rabies vaccination: Only participants randomized to EARLY rabies vaccine attend Visits 2, 3, 4. Visit 2 occurs 8 weeks after Day 0; Visit 3 occurs 7 days after Visit 2; Visit 4 occurs 21 to 28 days after Visit 2 AND at least 14 days after Visit 3.

^b^ LATE rabies vaccination: Only participants randomized to LATE rabies vaccine attend Visits 8, 9, 10. Visit 8 occurs 47 weeks after Day 0; Visit 9 occurs 7 days after Visit 8; Visit 10 occurs 21 to 28 days after Visit 8 AND at least 14 days after Visit 9.

^c^ Day 0 is defined as the day screening occurs and the first research blood sample is collected. Inclusion/exclusion criteria evaluation for enrollment will be completed when PCR and measles IgG/IgM and HIV results are available, generally by Day 14. In cases where the clinical presentation is consistent with measles but the Day 0 tests (measles PCR and measles IgM) are negative or equivocal, an optional retest of the measles IgM can be done between Days 7 and 10. The guardian/parent will be informed of the need for a retest and asked to bring the child back to the clinic. Blood will be collected via finger stick for the retest and results will be available by Day 14. All potential participants (or guardian/parent) will be informed of eligibility status by a designated study staff by phone, if possible, prior to the Day 14 scheduled study visit or at the Day 14 scheduled study visit. Ineligible participants may be invited to the site to discuss test results and referral for measles vaccination if serum IgG and IgM are both negative.

^d^ Vital signs include temperature, heart rate, and respiratory rate; may be obtained prior to rabies vaccine administration, if clinically indicated.

^e^ MUAC in children 12 to 59 months old.

^f^ HIV testing for children younger than 24 months will be performed via PCR and repeated with Rapid Diagnostic Test (RDT) at end of study to adhere to national guidelines; HIV RDT will be performed at screening for participants 24 months and older and will not be repeated at end of study.

^g^ HIV and measles serum IgM/IgG results must be reviewed for eligibility confirmation prior to Day 14.

^h^ Blood will be collected for hemoglobin test via finger and/or heel stick. Hemoglobin and urine pregnancy rapid test results must be reviewed prior to venous blood sample collection.

^i^ Females of child-bearing potential must have a negative pregnancy test prior to enrollment and each rabies vaccine administration.

^j^ Optional photography of the skin rash and/or Koplik spots for documenting the phenotype of the signs of the potential cases.

^k^ Measles vaccination to be offered to ineligible participants and administered to eligible control participants (through the study or referral to Ministry of Health vaccination program) if serum and PCR measles IgG and IgM are both negative.

^l^ 5 mL is the maximum volume that will be obtained at each blood draw.

^m^ Vitamin A will be administered at D0 to all participants with clinical measles per WHO guidelines: 2 oral doses of 200,000 IU given 24 hours apart. The first dose will be administered at the study site and the second will be provided to the parent to be administered 24 hours later.

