# STUDY OBJECTIVES

The objectives for this study are:

| **OBJECTIVES** | **ENDPOINTS** | **JUSTIFICATION FOR ENDPOINTS** |
| --- | --- | --- |
| **Primary** | | |
| To determine if MeV infection induces a loss of pre-existing immunity (immune amnesia) to endemic pathogens at Week 13 after baseline in children in select African regions. | Mean change in a panel of antibody levels over 13 weeks as measured by multiplex serological methods (e.g. PhIP-Seq/VirScan or SeroChip) and targeted ELISAs for confirmation. | These methods detect antibodies against multiple diverse pathogens and epitopes and assess both neutralizing and non-neutralizing antibodies. |
| To determine the effect of MeV infection on immune response to a controlled immune stimulus (rabies vaccination) at early and late timepoints post-infection. | Proportion of subjects with rabies virus neutralizing antibodies (RVNA) titer ≥ 0.5 International Units per milliliter (IU/mL) as measured by rapid fluorescent focus inhibition test 14 days after the last PrEP regimen vaccination. | These tests will measure the immune response and functionality of antibodies raised against the rabies vaccine. |
|  | Proportion of subjects with an RVNA titer ≥ lower limit of quantification 5-6 weeks after the first rabies vaccine dose. |  |
|  | Geometric mean RVNA titer 5-6 weeks after the first rabies vaccine dose. |  |
| **Secondary** | | |
| To determine if there is an increase in healthcare system encounters in the year following enrollment in children with recent MeV infection compared to those without recent MeV infection. | Mean number of non-study sick visit healthcare system encounters during the 1-year follow-up. | Visits to the healthcare system for sick visits in the year following enrollment in children with recent MeV infection will help determine the clinical impact of the immune amnesia in an objective manner. |
| To determine if MeV infection induces a loss of pre-existing immunity (immune amnesia) to endemic pathogens at Week 52 after baseline in children in select African regions. | Mean change in a panel of antibody levels over 52 weeks as measured by multiplex serological methods (e.g., PhIP-Seq/VirScan or SeroChip) and targeted ELISAs for confirmation. | These methods detect antibodies against multiple diverse pathogens and epitopes. These represent the spectrum of both neutralizing and non-neutralizing antibodies. |
| **Exploratory** | | |

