# STATISTICAL CONSIDERATIONS

This is a prospective, observational, longitudinal study. Children with acute measles and a control group without measles will be enrolled and followed for 1 year to examine the impact of MeV on the immune system. The impact will be measured using laboratory techniques that can assess the changes in total antibody diversity to multiple pathogens.

A controlled immune stimulus consisting of the rabies vaccine will be given to all participants with half receiving vaccines shortly after enrollment (at Week 8; “early” group) and the other half receiving them at a later timepoint (Week 47; “late” group). Antibodies to the rabies vaccine will be measured 5 weeks after the first rabies vaccine. This will provide information on the development of the immune response following MeV when the immune system is challenged with a controlled stimulus. The administration of early and late rabies vaccine will be randomly assigned and stratified by measles, by country group, and by age group.

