## Sample Size Determination

The overall sample size will be 256 participants. We will accrue 128 acute measles participants (with half of these in age group 1-5 years and half in age group 6-15 years) and 128 control participants (with half in each age group).

Randomization to early and late rabies vaccine will be stratified by country, group, and age.

Power for comparison of rabies titers

The sample size calculation is based on detecting a difference in the rabies antibody geometric mean titer between the MeV and control groups. The rabies vaccine will be given to half of the participants at Week 8 and half at Week 47 post enrollment, and the rabies antibody titer will be measured 5-6 weeks after receipt of the first vaccine dose (Weeks 13 and 52, respectively). There will be a random assignment for receipt of rabies vaccination to the two timepoints with equal numbers in the acute measles young and old groups and control young and old groups. In this analysis only one measurement of rabies antibody titer per participant will be included and it will be the measurement 5 weeks after receiving the rabies vaccine.

The total study sample size will be divided into 8 cohorts stratified by measles status, age group, and rabies vaccine timepoint as outlined in Figure 1. The standardized difference that can be detected with 90% power using a 0.05 level two-sided test for different sample sizes by specific cohort are shown in [Table 2.](#_Table_2:_Standardized)

Table 2: Standardized detectable difference with 90% power using a 0.05 level two-sided test for different sample sizes.

| Sample size per specific cohort (total study sample size) | Comparison of MeV to control at either the early time point or late time point  (assume std=1) | Interaction between time and group.  Example: comparison of difference between early MeV and control vs late MeV and control  (assume std=(1^2^+1^2^)^.5^=1.4) |
| --- | --- | --- |
| 20 (160) | 1.05 | 1.47 |
| 30 (240) | 0.85 | 1.19 |
| 40 (320) | 0.73 | 1.02 |

The chosen sample size of 256 accounts for a 6.5% loss to follow up.

Power for multiplex serological methods for global antibody analysis (e.g. virscan):

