We also present sample size calculations to show detectable change over time between groups in the panel of antibody measurements. This analysis will compare change in the panel of measurements from baseline to the 3-month blood draw between groups. The panel will contain numerous measurements, so we will use a Bonferroni correction to control the study-wide error rate at p=0.05. To be conservative, we will assume 1000 comparisons and plan to maintain the alpha level at a two-sided 0.05 rate (thus the power calculations will be performed with alpha=0.025/1000). We will perform the analysis separately for children aged 1-5 years and those aged 6-15 years. Table 3 gives the detectable between-group standardized difference (difference/std) with 90% power for different samples sizes with the Bonferroni correction for multiple comparisons. Here we combine the early and late rabies randomization groups since the rabies vaccination should not affect the comparison of other antibodies.

Table 3. Detectable standardized differences with 90% power.

The sample size is the number needed in an arm (measles or control), age group (young vs old (multiply by 4 for total sample size)

| Sample size per arm (total study sample size) | Standardized detectable difference |
| --- | --- |
| 40 (160) | 1.26 |
| 60 (240) | 1.00 |
| 80 (320) | 0.86 |

Note: The detectable difference of 1.00 that can be seen with a sample size of 240 is well within what the Mina paper found and is a reasonable sample size for this study.[[12](#_ENREF_12)]

Power for medical visit endpoint.

A particularly important secondary endpoint is healthcare encounters. We have calculated the power to compare health care encounters between the MeV and control groups for the selected sample size. One method to summarize healthcare encounters is to look at the proportion of participants in each group that had at least one medical visit. Using this measure, there would be 90% power to detect a difference in proportions of 0.5 versus 0.7 (control group versus MeV group, respectively) using a test of proportions. Note a proportion of 0.5 for the control group was used since this proportion gives the largest variance. Any larger or smaller proportions will allow smaller difference in proportions to be detected with 90% power. In the analysis, the Poisson test may be used which would be more powerful if participants have multiple healthcare encounters.

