### Analysis of Secondary Endpoints

The proportion of participants hospitalized between groups will be reported, exact conditional tests will be performed, and 95% Wilson score CIs will be calculated. A Poisson analysis will be used to compare the number of encounters with medical providers between groups. The average number of encounters per group per person will be calculated and compared. Since each person will have 1 year of follow-up, this would be appropriate. If participants drop out, we will adjust for time in study for each person.

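### The post-series blood draw is not tied to dose 3, so it can fall 7 to 17 days after the last dose, while a primary rabies endpoint is defined at 14 days

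*Protocol*

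**What the plan says.** Section 3 lists three rabies endpoints under the second primary objective. The responder proportion (RVNA ≥ 0.5 IU/mL) is counted from the last dose: "as measured by rapid fluorescent focus inhibition test 14 days after the last PrEP regimen vaccination". The other two, the proportion above the quantification limit and the titre itself, are counted from the first: "Geometric mean RVNA titer 5-6 weeks after the first rabies vaccine dose".

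Table 1 (Section 1.3) puts dose 1 at Week 8 (±3 days) in the early arm and Week 47 (±3 days) in the late arm. Dose 2 is a week later (+2 days). Dose 3 is at Week 11-12 or Week 50-51. Footnote a adds, for the early arm, "Visit 4 occurs 21 to 28 days after Visit 2 AND at least 14 days after Visit 3", and footnote b gives the same rule for Visits 8 to 10. Research blood is taken at Day 0, Day 14, Week 13 (+3 days) and Week 52 (+3 days). The sample following the series is therefore Visit 5 in the early arm and Visit 11 in the late arm. Section 8.2 uses one titre per participant, from that visit.

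**The concern.** One draw has to serve two clocks, one started by dose 1 and the other by dose 3. Dose 3 may fall on any of eight days after dose 1, and the draw does not move with it. The two clocks agree only when dose 3 is given at the start of its window. A child vaccinated later in the window, with every visit in order, has no sample at the time the endpoint names. The responder proportion is then read at an interval set by when dose 3 happened to be given. An analysis window written later can classify such samples, but it cannot supply one that was never drawn.

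**Working it through.** **Inputs** (Table 1, footnotes a and b, Section 3), counting from Day 0:
- Dose 1: Day 56, window Days 53-59 (late arm Day 329, window 326-332).
- Dose 3: 21 to 28 days after dose 1. I read Week 11-12 as Days 77-84 (late arm 350-357).
- Draw: Days 91-94 (late arm 364-367).
- Required gap from dose 3 to draw: 14 days.

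**1. The plan's own figure.** Gap = draw day − dose 3 day. With dose 1 on Day 56, dose 3 at 21 days (Day 77) and the draw on Day 91, the gap is 91 − 77 = 14. The 14 days is reproduced for this one choice of dose 3 day with the draw on target.

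**2. Dose 1 on target, every permitted dose 3 day.**

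| Dose 3, days after dose 1 | Study day | Gap, draw on Day 91 | Gap, draw on Day 94 |
| --- | --- | --- | --- |
| 21 | 77 | 14 | 17 |
| 22 | 78 | 13 | 16 |
| 23 | 79 | 12 | 15 |
| 24 | 80 | 11 | 14 |
| 25 | 81 | 10 | 13 |
| 26 | 82 | 9 | 12 |
| 27 | 83 | 8 | 11 |
| 28 | 84 | 7 | 10 |

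The range is 7 to 14 days with the draw on target and 7 to 17 over the whole draw window. For dose 3 on Days 81-84 the longest possible gaps are 13, 12, 11 and 10 days, so 14 is out of reach.

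**3. Dose 2 given 2 days late.** Dose 2 is then on day 9, and the 14-day spacing rule moves the earliest dose 3 to 9 + 14 = 23 days (Day 79). The longest gap with the draw on target is 91 − 79 = 12 days.

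**4. Dose 1 within ±3 days, dose 3 on Days 77-84, dose 2 on day 7.** The extremes are unchanged: 91 − 84 = 7 and 94 − 77 = 17. The number of dose 1 days compatible with dose 3 on Days 77, 78, …, 84 is 4, 5, 6, 7, 7, 6, 5, 4, which is 44 pairs. With four draw days each, that gives 44 × 4 = 176 combinations.
- Pairs that cannot reach 14 days on any draw day (dose 3 on Days 81-84): 7 + 6 + 5 + 4 = 22 of 44.
- Combinations outside an assumed 14 ± 3 days: for dose 3 on Days 81, 82, 83 and 84, respectively 1, 2, 3 and 4 of the four draw days give a gap below 11. The count is 7×1 + 6×2 + 5×3 + 4×4 = 50, and 50/176 = 28%. No gap exceeds 17, so all 50 are early.

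**5. Late arm.** Dose 1, dose 3 and draw are all shifted by 273 days, so every figure is the same. The unreachable dose 3 days are 354-357.

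**The case against.** The strongest reply is that the intended schedule is coherent: doses on days 0, 7 and 21 and a draw on day 35 put the sample 14 days after dose 3 and 5 weeks after dose 1. The departure comes only from the allowance for dose 3 on days 22 to 28. That is true, but the allowance is part of the schedule, and the draw was not made to follow it.

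A second reply is that 14 days is nominal and that the manual of procedures or the SAP, neither at hand, may set a tolerance. This stands against any count that treats day 13 as a failure. A reader might infer that 72% of samples would miss the endpoint, since 126 of the 176 combinations give fewer than 14 days. That figure presumes zero tolerance and equal use of every permitted day, and the documents support neither. The reply does not remove gaps of 7 to 10 days.

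Two other stronger readings also fail. A reader might infer a range of 4 to 20 days from the footnotes. That takes the ±3 days for dose 1 from Table 1's timepoint row while ignoring the Week 11-12 entry in the same row. A reader might also count draws 32 to 34 days after dose 1 as missing the 5-6 week endpoints. On target the draw is 35 days after dose 1, and being up to 3 days short is ordinary visit slack.

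Finally, the consequence is limited. Section 8.2 sizes the study on the geometric mean titre counted from dose 1, the second hypothesis in Section 8.1 concerns titre, and cases and controls follow one schedule. I accept all of this. A differential bias between cases and controls might be inferred, but nothing in the protocol shows one.

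**Conclusion.** The point holds, within limits. The schedule and the responder endpoint contradict each other as written: the sample is permitted at 7 to 17 days after dose 3, and the later half of the dose 3 days (with dose 1 on target) can never give the 14 days that Section 3 names. That statement needs no weighting of days. The 28% outside a 14 ± 3 day window rests on three assumptions: the tolerance itself, equal weight for each permitted combination, and Week 11-12 read as Days 77-84. It describes what the schedule allows and does not forecast practice. Figure 2 is not shown; the visible text contains no rule linking the draw to dose 3. The defect concerns the timing of one of three primary rabies endpoints and should be corrected, but it does not undermine the sample size or the comparison of titres.

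**What to change.** In footnotes a and b, set dose 3 at 21 to 25 days after the actual dose 1 date and at least 14 days after dose 2. Set the post-series draw (Visit 5 in the early arm, Visit 11 in the late arm) at 14 days (+3) after the actual dose 3 date. Every such draw is then 14 to 17 days after dose 3. It is also 21 + 14 = 35 to 25 + 17 = 42 days after dose 1, so one sample serves all three endpoints. If dose 3 is missed, draw 35 to 42 days after dose 1.

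Amend the Table 1 headers to match: dose 3 on Days 74-84 (late arm 347-357) and the post-series draw on Days 88-101 (late arm 361-374). Visit 5 in the late arm and Visit 11 in the early arm stay as they are.

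No visit, dose or sample is added. The costs are:
- The dose 3 window falls from 8 days to 5. If dose 2 is 2 days late, it falls to 3 (days 23-25), against 6 now (days 23-28).
- The just-vaccinated arm's antibody-panel draw has a wider window than the other arm's, at Week 13 (early arm) and at Week 52 (late arm). Section 8.2 pools the arms for the panel: "Here we combine the early and late rabies randomization groups since the rabies vaccination should not affect the comparison of other antibodies". Cases and controls should be affected alike, because of the randomisation: "The administration of early and late rabies vaccine will be randomly assigned and stratified by measles, by country group, and by age group".
- The late arm's last visit can fall before or after Day 364, so encounters need a cut at Day 364 or the adjustment that Section 8.5.3 already foresees: "If participants drop out, we will adjust for time in study for each person".

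If the sponsor prefers to leave the visits unchanged, restate the responder endpoint at about 5-6 weeks after dose 1, as Section 8.2 does for the titre, and report the actual interval from dose 3. This costs only wording, but the interval from dose 3 would still vary between 7 and 17 days.
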